## Abstract

The detection of molecular alterations is crucial for the individualized treatment of advanced non-small cell lung cancer (NSCLC). Missing targetable alterations may have a major impact on patient’s progression free and overall survival. Although laboratory testing for molecular alterations has continued to improve; little is known about how biopsy technique affects the detection rate of different mutations. In the retrospective study detection rate of epidermal growth factor (EGFR) mutations in tissue extracted by bronchoscopic cryobiopsy (CB was significantly higher compared to other standard biopsy techniques. This prospective, randomized, multicenter, single blinded study evaluates the accuracy of molecular genetic characterization of NSCLC for different cell sampling techniques. Key inclusion criteria are suspected lung cancer or the suspected relapse of known NSCLC that is bronchoscopically visible. Patients will be randomized, either to have a CB or a bronchoscopic forceps biopsy (FB). If indicated, a transbronchial needle aspiration (TBNA) of suspect lymph nodes will be performed. Blood liquid biopsy will be taken before tissue biopsy. The primary endpoint is the detection rate of molecular genetic alterations in NSCLC, using CB and FB. Secondary endpoints are differences in the combined detection of molecular genetic alterations between FB and CB, TBNA and liquid biopsy. This trial plans to recruit 540 patients, with 178 evaluable patients per study cohort. A histopathological and molecular genetic evaluation will be performed by the affiliated pathology departments of the national network for genomic medicine in lung cancer (nNGM), Germany. We will compare the diagnostic value of solid tumor tissue, lymph node cells and liquid biopsy for the molecular genetic characterization of NSCLC. This reflects a real world clinical setting, with potential direct impact on both treatment and survival.

## 1. Background

Lung cancer is one of the most common cancers, with 230,000 new diagnoses per annum in the United States and 410,000 in Europe, with a prevalence of approximately 1.8 million patients worldwide [1,2,3,4]. Non-small cell lung cancer (NSCLC) accounts for 75–85% of all lung cancers [5]. Two thirds of these patients are diagnosed in non-curable stage III or IV, and are usually treated systemically [6,7,8]. During the last decade, the systemic treatment has developed from a monomorphic platinum-based chemotherapy to a broad spectrum of individually tailored therapeutic approaches, based on the molecular tumor characterization of each patient [9]. NSCLC characterization is aligned to the existing specific therapeutics, but there are now rapidly developing new treatment options [10]. Patients’ individualized treatment becomes more effective, not only because of the broader therapeutic spectrum, but also with the increase of progression free and overall survival (in certain situations) [11,12,13,14,15,16,17,18]. In addition, side effect profiles are better for most targeted drugs compared to the earlier chemotherapy [12,13,14,19,20,21]. However, detection of a distinct mutation, aberration or translocation of the tumor cells and the evidence of a specific immunoreactivity, as determined by the expression of programmed death-receptor 1 (PD-1) and its ligand (PD-L1) on tumor cell surface (PD-L1) or patients’ T-cells (PD-1), are crucial to predict therapeutic effectiveness. So, the detection of a targetable structure predicts therapeutic response and therefore opens up the therapeutic window that would otherwise stay closed.

As a consequence, precise and correct characterization of the molecular genetic profile in patients with non-curable advanced stage III and IV NSCLC is crucial for ensuring optimal treatment; missing any targetable alteration may result in suboptimal therapy and could even impair patients’ overall outcome. Molecular genetic tumor characterization may also be of importance in earlier tumor stages.

Although tumor analytics are claimed to be refined and sensitized down to a single cell level, thus enabling facilitated tumor detection and characterization in the peripheral blood [22], the clinical relevance of this approach analyzing a huge number of cells is unclear. Furthermore, the detection of a single tumor cell type does not necessarily reflect the tumor, with its inherent heterogeneity, since NSCLC tumor heterogeneity has been known and characterized in various studies for a long time [23,24,25,26,27,28,29,30,31,32,33,34]. However, such considerations have rarely been addressed in therapeutically oriented studies. More stringent tumor tissue requirements as a basis for tumor characterization have, up to now, been only vaguely specified or not specified at all, even in large studies or international guidelines [10,35,36,37]. So, there is a definite need to optimize tissue analytics to provide representative tumor characterization; but there is also currently a lack of a ‘gold standard’ for evaluation of this approach [38]. Although large tumor specimens are generally preferred for mutation assays [36]; the required sample size has not been evaluated in the past.

Cryobiopsy (CB) has already been confirmed to be superior to forceps biopsy (FB) for histopathological evaluation of endobronchial malignancies in a prospective study [39]. A retrospective study [40] has confirmed that there is a significant increase in epidermal growth factor (EGFR) detection rate for CB compared to FB, but CB and FB have not yet been compared in terms of molecular genetic tumor characterization. Therefore, we have designed the PROFILER study to compare both bronchoscopic tissue sampling techniques (CB and FB), transbronchial needle aspiration (TBNA) and liquid biopsy for their diagnostic yield in NSCLC.

## 2. Methods/Design

### 2.1. Trial Design

The PROFILER study is a prospective, multicenter, randomized, single blinded trial in accordance with the German Medical Association Professional Code. It has been designed to evaluate the accuracy of molecular genetic characterization of NSCLC, with the primary aim being to detect the best biopsy technique for tumor cell profiling. Five university hospitals or lung cancer centers across Germany will participate in the study. The enrolment of 356 evaluable patients is planned (Figure 1) with 178 patients having either CB or FB. Based on the study protocol Version 2.9, this study is currently recruiting (the first subject being enrolled on 19 December 2018). The PROFILER study has been registered on www.clinicaltrials.gov; NCT03971175.

### 2.2. Patient Selection

Patients with primary diagnosis of suspected, centrally localized lung cancer, or patients with known NSCLC and suspected relapse after therapy, form the study population. Inclusion and exclusion criteria are shown in Table 1A,B.

### 2.3. Study Objectives

The primary objective is to assess differences in detection of molecular genetic alterations in NSCLC between FB and CB (Figure 2).

The secondary objectives assess differences in the detection of molecular genetic alterations in NSCLC between liquid biopsy, solid tumor tissue biopsy obtained by bronchoscopic techniques, cytological material obtained by TBNA, and to compare combined methods (tissue biopsy, TBNA and liquid biopsy) with single techniques, to evaluate differences between naïve and processed tumor tissue specimens (e.g., by microdissection), and finally, to assess differences in side effects (e.g., peri-interventional bleeding). 

The exploratory objectives analyze tumor mutational burden with regard to solid tumor tissue by FB or CB and cytologic material by TBNA and liquid biopsy.

### 2.4. Pre-Procedural Training and Standardization

All centers are already expert in the use of both forceps and cryobiopsy. Due to the integration or affiliation to the national network for genomic medicine lung cancer in Germany (nNGM), all participating pathologists will use the same standard for evaluation. 

### 2.5. Procedural Protocol

#### 2.5.1. Patient Enrollment 

The local investigators pre-screen any potential participant with pulmonary lesions which were suspicious of lung cancer, or known NSCLC with suspected relapse or progression, in accordance with the inclusion and exclusion criteria; after giving informed consent, patients are eligible for study entry. Bronchoscopy is undertaken according to local standards, and in accordance with the published guidelines [41,42]. If endobronchial tumor is visible and reachable, inclusion criterion 4 is fulfilled, and the patient can be included in the study. A study flow chart is shown in Figure 1.

#### 2.5.2. Randomization

Patients are randomized to either FB or CB for tissue sampling by a stratified, balanced (1:1) block randomization, stratified by study site. The randomization will be prepared at the Institute of Epidemiology and Medical Biometry, University of Ulm. Sealed envelopes will be prepared for use in every study site, containing the randomized group. The opening of an envelope has to be documented in detail on the case report form (CRF). Liquid biopsy is performed in every patient included in the study, and TBNA is performed if indicated, depending on local investigators’ decision, irrespective of randomization.

#### 2.5.3. Liquid Biopsy Procedure

Prior to any bronchoscopic intervention, blood is drawn for liquid biopsy analysis.

#### 2.5.4. Bronchoscopy

Bronchoscopy is performed using either a flexible or rigid technique, depending on the operator’s choice. In the case of flexible bronchoscopy, placement of an endotracheal tube is recommended in order to provide a secure airway. When rigid bronchoscopy is used, a tissue biopsy is carried out using a flexible bronchoscope inserted through the rigid tube. General anaesthesia will be used for rigid bronchoscopy, and deep sedation and local anaesthesia for intubation with a flexible tube. Patients will be monitored for oxygen saturation, ECG and repeated non-invasive blood pressure, according to the local standards of each center.

#### 2.5.5. Forceps and Cryobiopsy Procedure

Depending on randomization, forceps or cryobiopsy are performed, in accordance with the guidelines and previous reports [39,41,42,43,44]. Forceps of a diameter between 1.8 and 2.6 mm are used for FB; cryoprobes of 1.9 or 2.4 mm (Erbe Elektromedizin GmbH, Tübingen, Germany) are used for CB. Freezing time for CB is dependent on the individual situation, morphology, localization, size and probe positioning, and is determined by the local investigator. A minimum of four biopsies will be taken.

#### 2.5.6. TBNA Procedure

If indicated, TBNA is performed, preferentially under EBUS- guidance, to evaluate hilar and mediastinal lymph node metastasis. In some cases, TBNA may be done without EBUS guidance. EBUS equipment is not predefined by the study protocol; the procedure being performed according to the local standard and guidelines [45,46].

### 2.6. Pathological Analysis

#### 2.6.1. Baseline Pathological Evaluation

The histological, immunohistological and immunohistochemical evaluation of extracted solid tissues by FB or CB, and the cytological, immunocytological and immuncytochemical evaluation of TBNA extracted cytoblock or smear, are performed at the local pathological institute (including ALK, ROS 1 and PD-L1 expression level on tumor cells). Histological and immunohistological tissue evaluation, or cytological and immunocytological evaluation, assigns the tumor tissue to either NSCLC or small cell lung cancer (SCLC). Any cases of SCLC will be excluded from further analyses and classified as a ‘drop out’. For any NSCLC, further molecular genetic evaluation will be undertaken, as described below.

Harmonization of the analytical processes is guaranteed in the study setting by the choice of the individual institutes of pathology, which are partners in the German national network of genomic medicine lung cancer (NGM lung cancer) [47], or which have participated in national collaborative ring trials. Additional collaborative ring trials for the analytical process will be performed for a selection of samples prior to the planned analytical process in this study.

#### 2.6.2. Molecular Genetic Evaluation

Molecular genetic testing will be performed for solid bronchoscopically extracted material, for the cytological specimen extracted by TBNA (if applicable), and for the liquid biopsy samples. All currently targetable and non-targetable genetic aberrations, as suggested by the guidelines [10,35,36,37] (mutations, fusions, copy number variation (CNV)), as well as other important prognostic markers, are analyzed in accordance with the guidelines for standardized evaluation from the nNGM lung cancer consortium [48]. Targeted multigene mutation screening will be performed using different next generation sequencing techniques and platforms, depending on the participating site:

Tübingen: Amplicon library preparation will be done using the nNGM Panel 1.0 and 2.0. Semiconductor sequencing will be performed according to the manufacturers’ manuals using the Ion AmpliSeq Library Kit v2.0, the Ion 510 and Ion 520 and Ion 530 Kit—Chef and the Ion 520 Chip Kit on the Ion GeneStudio S5 (Ion Reporter software) (Thermo Fisher Scientific, Waltham, MA, USA). Fusion and CNV detection will be undertaken with immunohistochemistry following fluorescent in situ hybridization, or with the Archer^®^ FusionPlex Lung panel (Archer Analysis software, ArcherDX, Boulder, CO, USA).

Hamburg: The NEOselect assay (NEO New Oncology, Cologne, Germany) is used to detect single nucleotide mutations, copy number variations and fusions on the Illumina NextSeq system (Illumina, San Diego, CA, USA), according to the manufacturers’ manual. In the case of very limited material, CNVs will be tested using PCR technologies such as cobas^®^; fusion and CNV detection will be undertaken with immunohistochemistry.

Köln: The amplification of DNA will be performed using the customized GeneRead DNAseq custom Panel V2 with primers for the nNGM Panel 1.0 and 2.0 (Qiagen, Hilden, Germany), following the manufacturer’s instructions. For library preparation, the Gene Read DNA Library I Core Kit and the Gene Read DNA I Amp Kit (Qiagen) will be used. After end-repair and adenylation, libraries were ligated to NEXTflex DNA Barcodes (Bio Scientific, Austin, TX, USA) and sequenced on the MiSeq (Illumina, San Diego, CA, USA) with a MiSeq reagent kit V2 (300 cycles) (Illumina), following the manufacturer’s recommendations. Data will be exported as FASTQ files. Alignment, variant calling and annotation will be done using an in-house bioinformatic pipeline. A 5% cutoff for variant calls will be used, and results will only be interpreted if the coverage was >200×. The detection of gene fusions will either be done by a combination of immunohistochemistry and fluorescence in situ hybridization (FISH), or by using the Archer^®^ FusionPlex Lung panel with the Archer Analysis software (ArcherDX, Boulder, CO, USA). CNVs will be analyzed by FISH.

Essen: The QIASeq Targeted DNA Panels (Qiagen, Hilden, Germany) nNGML1 and/or nNGML1.2 [48] will be run on an Illumina MiSeq or Illumina NextSeq platform, and the CLC Genomics Workbench versions 5.0.1, 12.0.3 or 20 will be used for data acquisition. Fusion and CNV detection will be carried out by immunohistochemistry, FISH, or by using Archer^®^ FusionPlex CTL panel (ArcherDX, Boulder, CO, USA).

### 2.7. Safety Data

#### 2.7.1. Bleeding

Bleeding is the most relevant side effect of any bronchoscopic biopsy and is categorized as shown in Table 2.

#### 2.7.2. Other side Effects

In addition to bleeding, hypoxia, cardiac arrhythmia, fever, infection and any other event attributable to the procedure will be evaluated.

### 2.8. Statistical Methodology 

All analyses will be performed by the independent Institute of Epidemiology and Medical Biometry, Ulm University, after database lock and unblinding. A comprehensive statistical analysis plan (SAP) will be prepared prior to a first analysis of the study data.

#### 2.8.1. Sample Size Estimate

Sample size calculation is based on the comparison of the detection rates for both techniques (FB and CB). Based on our earlier retrospective study, the cryobiopsy detection rate of EGFR was increased by approximately 50%, from 14% to 21% [40]. As our primary endpoint combines various aberrations, including PD-L1-expression level, a rate of detectable alterations of around 40% could be expected. With an expected relative increase of almost 50% for aberrations, related to a frequency of 40%, an absolute detection frequency of 55% was considered to be a conservative estimate.

The following assumptions were made for the sample size calculation: two-sided Chi-square test, type one error alpha = 0.05, power = 0.80. With a detection rate of 40% in the control FB group, and a conservative estimation of the detection rate of 55% in the experimental CB-group, and an assumption of equal number of patients in each group, 173 patients are required for each group, i.e., 2 × 173 = 346 patients in the whole trial.

Because of the short duration of observation in each patient, the rate of loss to follow up is very small. To allow a drop-out rate of up to 3% 10 extra patients need to be recruited, resulting in a total sample size of 356 patients. As seen in Figure 1, the sample size for recruitment has to be increased, because NSCLC is likely to form 80% of all tumors; about 45 will be small cell lung cancer (SCLC) and about 10% (25 cases) would not be diagnostic in each cohort. Therefore, 2 × 248 patients will be required for randomisation. Although there is no current data, it can be assumed that in some cases an endobronchial tumor will not be visible. As a rough estimate, we assume that in 8% of the cases (*n* = 44), it will not be possible to take a biopsy from the central airways. This therefore determines that the total number of recruited suspected lung cancer patients is 540.

Sample size calculation was performed by nQuery Advanced 8.1.

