#### 2.8.4. Primary Endpoint Analysis

The primary endpoint is the detection of at least one molecular genetic alteration in NSCLC. Confirmatory and exploratory data analyses are performed for this dichotomous primary endpoint as follows: 

The difference in both groups based on the primary endpoint are evaluated using a Chi-square test (two sided at a significance level of 5%). All further analyses of the primary endpoint will be performed in an exploratory fashion. All results from these analyses will be regarded as hypothesis-generating, and not as proof of efficacy. Univariate and multiple logistic regression models to adjust for strata (study site) and potential confounding variables will be performed.

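### The sample-size build-up implies that the primary comparison leaves out randomised patients with a non-diagnostic biopsy, although diagnostic failure is itself an outcome of the technique

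*Protocol article*

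**What the plan says.** Section 2.8.1 sizes the primary test with these settings: "two-sided Chi-square test, type one error alpha = 0.05, power = 0.80". The rates are given as "With a detection rate of 40% in the control FB group" and "a conservative estimation of the detection rate of 55% in the experimental CB-group". This yields 173 per group, raised to 178 for drop-out. The section then adds patients lost after randomisation, "about 45 will be small cell lung cancer (SCLC) and about 10% (25 cases) would not be diagnostic in each cohort", to reach 248 randomised per arm. Tumours that cannot be sampled in the central airways are a separate allowance of 44 patients, added on top of the 2 × 248.

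The Abstract describes the trial as one "with 178 evaluable patients per study cohort", and section 2.1 likewise plans 356 evaluable patients. Section 2.8.4 states: "The primary endpoint is the detection of at least one molecular genetic alteration in NSCLC". It names the test but no analysis set, and does not say how a failed biopsy is counted. Section 2.6.1 excludes SCLC explicitly and has no matching rule for non-diagnostic specimens.

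Section 1 states: "Cryobiopsy (CB) has already been confirmed to be superior to forceps biopsy (FB) for histopathological evaluation of endobronchial malignancies".

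**The concern.** The biopsy is the randomised intervention. Tumour histology exists before randomisation, so leaving out SCLC is in principle a restriction on a baseline trait. A non-diagnostic specimen is different: it arises after randomisation and is produced by the technique under test. If such patients leave the comparison, each arm is filtered by its own technique's success, and randomisation no longer protects the comparison.

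The plan assumes the same 10% loss in both cohorts, while its Background reports that CB does better for histopathological evaluation. If failure differs, the two evaluable groups need not be alike. The analysis would then answer which technique detects more once a usable specimen is in hand. The aim in section 2.1 is to find the best biopsy technique for tumour profiling, and a technique that more often yields nothing usable is worse on that aim. The confirmatory result is at stake.

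**Working it through.** **1. The plan's own figures.** Inputs from section 2.8.1: p1 = 0.40, p2 = 0.55, two-sided alpha 0.05, power 0.80, equal groups. With mean rate 0.475,

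n = [1.96·√(2·0.475·0.525) + 0.8416·√(0.40·0.60 + 0.55·0.45)]² / 0.15² = (1.3842 + 0.5876)² / 0.0225 = 172.8, so 173 per group. This matches. Power at 178 per group is 81.2%.

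**2. Where the non-diagnostic patients go.** 248 − 45 − 25 = 178, exactly the evaluable number. So 70 of 248 randomised patients per arm (28.2%) fall outside the set on which the test is sized. Of these, 25 are failures of the biopsy, or 25/203 = 12.3% of the 178 + 25 = 203 non-SCLC patients.

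**3. Effect on the difference.** Let f and c be the failure rates with FB and CB, and apply 40% and 55% to diagnostic specimens. Counting a failure as no detection, the rates are 0.40(1 − f) and 0.55(1 − c). The evaluable-only difference stays at 15.0 points. Only the equal 10% comes from the plan; the unequal pairs are assumptions, because the article gives no arm-specific rates.

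| FB / CB failure | Failures counted | Difference (points) | Evaluable-only (points) |
|---|---|---|---|
| 10% / 10% | 36.0% v 49.5% | 13.5 | 15.0 |
| 15% / 10% | 34.0% v 49.5% | 15.5 | 15.0 |
| 15% / 5% | 34.0% v 52.25% | 18.3 | 15.0 |
| 20% / 5% | 32.0% v 52.25% | 20.3 | 15.0 |

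The two analyses agree when 0.40f = 0.55c, that is f = 1.375c. Below that ratio evaluable-only overstates the CB advantage; above it, evaluable-only understates it.

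If detection in diagnostic specimens were 40% in both arms and failure 15% / 5%, evaluable-only would show 0 points. Counting failures gives 34% v 38%, or 4 points.

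**4. Effect on power.** Power = Φ{[δ − 1.96·√(2·p̄(1 − p̄)/n)] / √[(p1(1 − p1) + p2(1 − p2))/n]}.

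- *Keep only the NSCLC share of failures.* 248 × 0.80 ≈ 198 per arm (178 + 25 × 0.80), about 10% failure. Rates are 178 × 0.40/198 = 36.0% and 178 × 0.55/198 = 49.4%; power 77.6%; 211 per arm needed for 80%.
- *Keep all 25 failures.* 203 per arm, 12.3% failure. Rates 35.1% v 48.2%; power 76.9%; 220 per arm needed for 80%.
- *Assumed 15% / 5% failure, 198 per arm.* Power is 96% with failures counted and about 81% evaluable-only.

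**5. If 40% and 55% are read as rates in all 203 non-SCLC patients per arm.** Counting failures gives 15.0 points and 86% power. Evaluable-only with 15% / 5% failure gives 0.40/0.85 = 47.1% v 0.55/0.95 = 57.9%, or 10.8 points and about 54% power. With equal 10% failure it gives 44.4% v 61.1%, or 16.7 points.

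**The case against.** The strongest reply is that no section defines the analysis set. The sentence on SCLC and non-diagnostic cases is a recruitment allowance, a SAP is announced in section 2.8, and the flow chart is not shown. This stands in part: a reader might take the article to state a rule excluding failed biopsies, and it does not. But the point does not rest on silence. The article commits to 178 evaluable per arm and sizes the test on them; a SAP that counted failures would depart from that published basis.

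Second, section 2.6.1 lets cytology assign a tumour to NSCLC, so a patient with a failed FB or CB and a positive TBNA might stay in as a non-detection. Some of the 25 may also not have NSCLC. Both are possible, and the article does not settle either.

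Third, detection in confirmed NSCLC fits the wording of the endpoint. That is a legitimate question, but confirmation that depends on the randomised biopsy still selects by technique.

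Three stronger readings are tempting and unsupported:

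- *The bias works against CB.* The plan's own equal 10% failure gives the opposite direction. Section 1 supports unequal failure only qualitatively, without rates.
- *Exclusion removes the main way CB could help.* The rationale also rests on tumour heterogeneity and larger specimens, and those advantages can appear among diagnostic specimens.
- *Patients with uninterpretable sequencing are dropped too.* The statement "A 5% cutoff for variant calls will be used, and results will only be interpreted if the coverage was" a given depth is one site's reporting threshold in section 2.6.2. It does not say that such patients leave the analysis.

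**Conclusion.** The concern holds as a risk of selection bias built into the planned primary comparison. The sample-size arithmetic is sound; the weakness is the population it implies. Under the plan's equal 10% failure, evaluable-only overstates the patient-level difference by 1.5 points (15.0 v 13.5). Under an assumed 15% / 5% it understates it by about 3.3 points (15.0 v 18.3). The direction therefore depends on arm-specific failure rates that the article does not give. All these figures take 40% and 55% as rates in diagnostic specimens and count every failure as a non-detection. With failures counted and losses as planned, power is about 77–78%. That is 2–3 points below the stated 80% and 3–4 points below the 81% available at 178 per arm.

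**What to change.** Before unblinding, state in the protocol or SAP that:

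- the primary set is all randomised patients, by randomised arm, excluding only those with a confirmed diagnosis of SCLC or another non-NSCLC condition from any routinely available specimen;
- a non-diagnostic or insufficient randomised biopsy counts as no alteration detected;
- patients who remain undiagnosed stay in the denominator;
- the evaluable-only comparison is a sensitivity analysis;
- power is about 77–78% at 198–203 per arm with equal 10–12% failure, and higher if CB fails less often.

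The cost is wording, plus recording the final routine diagnosis for about 50 patients (2 × 25); the article describes no such collection. No extra procedure is needed. If the sponsor wants to hold 80% under equal failure, the analysis set must grow to 211–220 per arm, that is 13 to 17 more per arm (211 − 198; 220 − 203). Otherwise the small loss of power should be accepted and stated.
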